## Abstract

**Background::**

Internet-based rehabilitation can ease the progression of chronic diseases. There had been studies on internet-based rehabilitation of knee osteoarthritis (OA), but them were conducted at home and ignored the potential benefits in the community setting. This study will explore the feasibility and effectiveness of internet-based rehabilitation accompanies wearable devices in the community setting for the patients with knee OA.

**Methods::**

An assessor-blinded randomized controlled feasibility trial will be performed to study the feasibility and effectiveness of internet-based rehabilitation program for the patients with knee OA in the community setting. Forty participants with knee OA will be recruited and randomly allocated into internet-based rehabilitation group (IRG) or control group (CG). The interventions of IRG will be performed in the community setting via web-based platform and wearable devices. The outcome measures will be conducted at baseline, and post-intervention 6 weeks, 12 weeks during the study. The feasibility will be tested by the proportion of participants who will complete the internet-based rehabilitation program within 12 weeks in IRG as well as the compliance and satisfaction. Additionally, the effectiveness of internet-based rehabilitation will be assessed by the Western Ontario and McMaster Universities Osteoarthritis Index, 11-point Numerical Rating Scale and Short Form-36 quality-of-life questionnaire.

**Conclusion::**

The internet-based rehabilitation program and community-based interventions is feasible and efficacy to ameliorate the osteoarthritic pain and promote the physical function and quality of life for the patients with knee OA in the community setting.

**Trial registration number::**

The study was registered in the clinical trial registry ChiCTR2000033397.

## Introduction

1

Osteoarthritis (OA) is a chronic, debilitating and degenerative joint disease, and widely considered as a significant threat to healthy aging.^[1]^ It has been reported that nearly 250 million individuals suffered from OA in the world, of which the prevalence of knee OA is the highest, accounting for 16–17% in the population aged from 50 to 75 years.^[2]^ The chronic pain and physiological dysfunction are considered to be the main problems of the patients with knee OA.^[1,3]^ To address these issues and control the progression of OA, lifestyle modification is one of the effective strategies universally recommended in the guidelines of OA. The lifestyle modification includes the physical fitting exercise, self-management of behavior, and efficient learning of osteoarthritis-related knowledge.^[4–6]^ Physical fitting exercise, such as aerobic exercise and strength training, plays an important role in balancing cytokine dynamics in the synovial fluid and inhibiting inflammatory reaction and oxidative stress.^[7,8]^ Self-management is one of the biopsychosocial models to promote the adherence to OA treatment through behavior change and psychosocial coping skills, which include the behavioral, role and emotional managements.^[9,10]^ The education of osteoarthritis-related knowledge is necessity for patients subjected to knee OA, which have been demonstrated to improve the quality of life and coping skills.^[11,12]^

It is a challenge to perform the lifestyle modification strategy to individuals with knee OA when they are discharged from health care setting.^[13,14]^ The lack of professional supervision and feedback would result in the decline of participation in continuous medical or rehabilitative services of OA, which will subsequently decrease the efficacy of OA treatments at home or in the community setting.^[15,16]^ Moreover, few medical facilities and resources could be accessible in the rural areas, where the elder had been reported to have poor health-related quality of life.^[17]^

With the development of telemedicine, patients living in remote areas could obtain a chance to perform a real-time communication with the professional physicians. The concept of telerehabilitation in the field of physical medicine and rehabilitation has been put forward, which combines telemedicine with rehabilitation interventions to provide support for the continuous rehabilitative services for the disabled patients.^[18]^ Of which, the internet-based rehabilitation is one of effective strategies in telerehabilitation, and its feasibility and effectiveness have been explored.^[19,20]^ The combination of an internet-supported program of constraint-induced therapy (LifeCIT) and a wearable real-time muscle kinematics device has been tested to improve the upper limb function and quality of life for people after stroke.^[19]^ Furthermore, internet-based rehabilitation was found to effectively reduce hospital admissions according to the summary of 47 eHealth applications used in Dutch COPD care.^[20]^ Internet-based rehabilitation had also been applied in the monitor, guidance and treatment of Parkinson's disease, post-knee arthroplasty and multiple sclerosis.^[21–23]^

Several studies have been conducted to explore the feasibility and effectiveness of the internet-based rehabilitation for individuals with knee OA, including the “Join2Move”, “PainCOACH” and “Help My Knees” programs.^[24–26]^ The compliance of internet-based rehabilitation varied in the previous studies, and appeared to be dependent on the education level and willingness of participants, as well as whether the remote-control reminder such as email, telephone or messages was set up during the study.^[25]^ It is therefore necessary to explore the feasible and effective way to improve the acceptability and adherence of internet-based rehabilitation for the patients with knee OA. Whilst the comparison of function and pain-relief was not significant between the internet-based rehabilitation and control groups, the programs based on the progressive lower-limb strength training, flexibility and walking exercise were shown to improve the function and ameliorate the osteoarthritic pain.^[26–28]^ The optimal design of modules with regard to the lifestyle modification in the internet-based rehabilitation programs should be taken into account for the patients with knee OA.

Community-based rehabilitation is a continuous rehabilitation model for patients with knee OA and it is also an important link from family to society.^[29]^ The World Health Organization had asserted the importance of enhancing the participation of people with disabilities in the daily life and social activities based on the International Classification of Functioning, Disability and Health framework.^[30]^ Participation is regarded as a vital outcome in community-based rehabilitation.^[31]^ Patients can reduce the sense of shame caused by diseases and build up confidence in a recognized or accepted environment, so as to promote the healthy development of physiology and psychology.^[32]^ It is also recognized that the development of community-based rehabilitation could facilitate the management of chronic diseases, in particular for OA.^[33]^ However, the insufficient number of healthcare providers in the community setting impeded the development of community-based rehabilitation for patients with OA.^[33,34]^ Researches showed that community-based rehabilitation could create a mutual supervision environment for patients and improve their compliance.^[35,36]^ In addition, wearable devices also promote the monitor of patients function and advance the community-based rehabilitative service, conveniently collecting data and giving feedback to clinicians.^[37,38]^ Up to date, there have been few studies published in China regarding the effect of internet-based rehabilitation on the continuous intervention for the patients with OA in the community setting. It is desirable to explore the optimal strategy of internet-based rehabilitation programs to improve the pain and physical function of the individuals with OA through the coordination of community-based rehabilitation in this study.

Therefore, the purpose of this randomized controlled trial is to explore the feasibility and effectiveness of combining the internet-based rehabilitation with the community-based interventions and resources for the patients with knee OA. To achieve the connecting effect by means of internet technology within the community setting, a specific software “FOR KOA” was purposely designed, which can be installed in the mobile phone and is capable of collecting the basic information of the participants recruited in this study, and monitoring the change of heart rate, blood pressure and oxyhemoglobin saturation from bracelet. The community-based interventions including and aerobics (power cycling and walking) and strength training. The hypothesis is that this collaborating strategy of the internet-based rehabilitation program and community-based interventions is feasible and efficacy to ameliorate the osteoarthritic pain and promote the physical function and quality of life for the patients with knee OA in the community setting.

## Methods

2

### Study design

2.1

The study is a 12-week, assessor-blinded randomized control trial, following the standard protocol: Recommendations for Interventional Trials (SPIRIT) guidelines.^[39]^ Meanwhile, the report will be presented as the CONSORT and TIDieR guidelines.^[39–42]^ The flow chart of the clinical trial is shown in Figure 1. Trial recruitment started on the 15^th^ June 2020. Completion of interventions and closure of the data set is planned for early spring of 2021.

**Figure 1 F1:**
[figure not shown]
The flow chart of the trial.

### Participant

2.2

#### Inclusion criteria

2.2.1

Eligible participants will meet the following requirements: diagnosed with knee OA according to the 2018 Chinese Orthopedics Association (COA) guidelines for diagnosis and treatment of knee OA which satisfy following (1) and two criteria from (2) or (3) or (4) or (5):^[43]^ (1) recurrent knee pain in the last month; (2) narrowed joint space, subchondral cyst formation and bone sclerosis, or osteophytosis around joint margin on the radiographs in standing or load position in X-ray; (3) aged 50 years and over; (4) stiffness no more than 30 minutes in the morning; (5) palpable bone crepitation (fremitus) on movement of joint. In addition, participants will have the ability to use smart phones, communicate in Mandarin and understand Chinese characters.

#### Exclusion criteria

2.2.2

Participants who meet any of the following criteria will not be able to participate in the trial: having other systemic rheumatic diseases that have been diagnosed at the knee; having fallen in nearly 6 months; ready for knee arthroplasty; all knee arthroplasty or other knee-related surgery were performed, and meniscal tear or anterior cruciate ligament (ACL) tear occurred in the past six months; there were other health problems that prevented them from participants were treated for knee OA in the past six months, including surgery, medication, and physical therapy; chronic kidney disease; cancer; dementia or severe cognitive impairment; mental illness; hospitalization for stroke, heart attack, heart failure, or surgery for arterial obstruction in the past three months; there were other health problems that prevented them from participating in the project; unable to sign informed consent. Table 1 lists the full eligibility criteria.

**Table 1 T1:**
[figure not shown]
Trial inclusion/exclusion criteria.

#### Recruitment

2.2.3

A multidisciplinary rehabilitative team has been built up, including the physicians, physiotherapists, nurses and bio-statistical professors. The potential participants will be recruited from the medical consultations in the 2 communities, supported by the department of rehabilitation medicine center of the Center of Rehabilitation Medicine, West China Hospital, Sichuan University. These communities had to previously signed the agreement with the West China Hospital of Sichuan University prior to study. The content will be explained to the patients from the community setting and they will be referred to a research staff responsible for collecting information for registration if they show interest in it. The research staffs are in charge of contacting the patients and making an appointment for medical evaluation. The eligible participants will be allocated into internet-based rehabilitation or control groups after the end of medical consultation. Furthermore, the recruitment can be performed through the Wechat app in the mobile to release the recruitment information. We will publish the details of the experiment in Wechat group, including the start time of the trial, the content to be carried out and the statement of relevant interests. People will fill out a spreadsheet to collect information if they are interested in this, and dedicated staffs will contact them for evaluation.

### Interventions

2.3

#### Internet-based rehabilitation group

2.3.1

The purposely designed software “FOR KOA” enable the conduct of the internet-based rehabilitation programs, which mainly include arthritis education, self-management and land-based exercise programs according to the latest guidelines by Osteoarthritis Research Society International (OARSI).^[5]^ The bracelet matched with the software “FOR KOA” will automatically collect the heart rate, blood pressure and blood oxygen saturation of the participants during the exercise and display them, so as to allow the physical therapist to remotely monitor whether the participants’ exercise intensity meets the requirements (The software “FOR KOA”: A and B of Fig. 2; The bracelet for patients: Fig. 3). Participants will also be required to assess the outcome from the software “FOR KOA” at the beginning of the trial, after 6 weeks and 12 weeks. Participants may terminate the trial at any time and receive relevant treatment in case of symptom deterioration or other unexpected circumstances during the trial. During the trial, the celecoxib and glucosamine hydrochloride are also required.

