### Randomization and blinding

2.4

Participants will be randomly divided into the internet-based rehabilitation group and control group as the proportion of 1:1 according to the principle of random distribution after completing the baseline assessment for participants. The random numbers will be generated via computer software programs designed by statisticians who is blinded to the study content. The random number assigned to each group will be written on a piece of paper and placed in a sealed and opaque envelope. The envelope will be provided to the participants based on the randomization order. The assessors in the trial will not be aware of the random assignment for the participants. All the physicians and physiotherapists participating in the outcomes assessment and intervention guidance will receive a standardized training prior to this study, and will be allocated into these different two procedures during the trial. Physicians and physiotherapists involved in the assessment will not participate in the later experimental intervention. Data will be analyzed with blinding to group allocation in the data statistics.

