### Outcome assessments

2.6

Outcomes assessments will be conducted at baseline, 6 weeks and 12 weeks post-intervention. All participants will be assessed by researchers who are blinded to the group assignment.

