#### Secondary outcome measures

2.6.2

Pain of knee (s) will be assessed with a 11-point Numerical Rating Scale, 0 is no pain and 10 is worst possible pain.

The Western Ontario and McMaster Universities Osteoarthritis Index (WOMAC) will be used to measure pain, stiffness and physical function in the knee. WOMAC, a self-administered health-status instrument for patients with knee OA, consists of 24 items within three subscales: pain (five items), stiffness (two items) and physical function (17 items).^[46,47]^ All items are rated on a Likert scale of 0 (no symptoms)–4 (extreme symptoms), with a total range of 0–96 and higher scores indicating worse symptoms.

Quality of life will be assessed by means of the Short Form-36 quality-of-life questionnaire (SF-36). Zero points corresponds to the worst quality of life and 100 points corresponds to the best quality of life as put forward through the questionnaire.^[48]^

Adverse events will be recorded throughout the trial. The intensity and possible relationship with the treatment will be examined and described in detail if those once occurred.

Baseline assessment will be carried out after eligibility and informed consent have been confirmed. Demographic data referring to participant's age (in years), gender, height, weight, body mass index (BMI), physical functional data referring to physical activity (evaluated by the International Physical Activity Questionnaire (IPAQ) short version),^[49]^ education, occupation, source of income, hobbies and interests, marital, smoking and drinking status, medical history will all be collected.

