### Data collection and management

2.10

The outcome and questionnaire data of IRG are stored on stored on secure servers Alibaba Cloud servers in China. The data of CG will be collected by CRF. Then, the CRF will be transcribed the into Alibaba Cloud servers by research assistants. Only the research team has access to the data. The details of data confidentiality and storage are included in the consent form and explained to participants by the research assistant during the baseline lab session. All information of the participants will be kept confidential and explained to them in the informed consent form. A formal data monitoring committee has not been created for this intervention; however, the project coordinator provides monthly reports on participant numbers and trial progress to the principal investigator. The final decision will be made by the principal investigator.

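### Outcome data are described as reaching the database by a different route in each arm, which is not reconciled with blinded assessment of all participants or with baseline before randomisation

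*Protocol article*

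**What the plan says.** All references are to the protocol article.

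- **Section 2.3.1 (Internet-based rehabilitation group).** "Participants will also be required to assess the outcome from the software" FOR KOA, at the beginning of the trial and after 6 and 12 weeks. Section 2.3.2 (Control group) has no counterpart.
- **Section 2.10 (Data collection and management).** For the IRG: "The outcome and questionnaire data of IRG are stored on stored on secure servers Alibaba Cloud servers in China". For the controls: "The data of CG will be collected by CRF", followed by "Then, the CRF will be transcribed the into Alibaba Cloud servers by research assistants".
- **Section 2.6 (Outcome assessments).** At baseline, 6 and 12 weeks, "All participants will be assessed by researchers who are blinded to the group assignment".
- **Section 2.4 (Randomization and blinding).** "The assessors in the trial will not be aware of the random assignment for the participants". Allocation takes place "after completing the baseline assessment for participants".
- **Section 2.6.2 (Secondary outcome measures).** "Pain of knee (s) will be assessed with a 11-point Numerical Rating Scale, 0 is no pain and 10 is worst possible pain". WOMAC is described as self-administered, and SF-36 is a questionnaire. All three are reported by the patient.
- **Section 2.9 (Statistical analysis).** These scores are analysed by repeated-measures analysis of variance with post-hoc tests, or by a rank sum test when the assumptions fail, at a 0.05 threshold.

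**The concern.** FOR KOA is not a neutral data-capture tool. It delivers the intervention and is the channel through which IRG participants communicate with their physicians and physiotherapists (sections 2.3.1.1 and 2.3.1.3). The Discussion adds that caregivers will be encouraged to assist and that staff may help participants use the software. If IRG participants rate pain, function and quality of life inside that channel while controls use a separate form, the conditions of measurement differ by arm as well as the treatment.

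The baseline has its own difficulty. Before randomisation nobody belongs to the IRG, so an assessment at the beginning that is specific to the IRG does not fit an order in which baseline precedes allocation. Either the app baseline follows allocation, or baseline is collected alike in both arms and the IRG changes mode afterwards, or there are two baseline records. The article does not say which.

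The trial's hypothesis about pain, function and quality of life rests on these scores, as do the between-group tests. So do the means and variability that section 2.8 wants to carry forward to a larger study.

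**Working it through.** **Step 1. The statements side by side.**

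| Question | IRG | CG |
|---|---|---|
| Where the participant assesses outcomes | FOR KOA app (2.3.1) | no app assessment described (2.3.2) |
| How outcome data are collected or held | cloud server, no CRF step described (2.10) | CRF, then transcribed to the server (2.10) |
| Who assesses | blinded researcher (2.6) | blinded researcher (2.6) |
| When the first assessment occurs | before allocation (2.4), but in an IRG-specific procedure (2.3.1) | before allocation (2.4) |

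The app time points in section 2.3.1 are the same three as in section 2.6, and section 2.10 refers to IRG outcome and questionnaire data. The natural reading is that the app entries are the NRS, WOMAC and SF-36 scores. That is an inference, because section 2.3.1 names no scale. On this reading all 20 IRG participants use one mode and all 20 controls the other, so there is no overlap from which a mode effect could be estimated.

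**Step 2. When a shift biases the comparison and when it cancels.** Let s(t) be the extra reporting shift in the IRG relative to the CG at time t.

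- Bias in a single follow-up comparison = s(t).
- Bias in the between-arm difference in change from baseline = s(t) − s(0).

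Three cases follow:

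- App in the IRG throughout and s constant: s(12) − s(0) = 0. The shift cancels in change scores and in the group-by-time term. It does not cancel in a post-hoc or rank sum comparison of a follow-up score alone.
- App in the IRG throughout, but s changes as participants become more engaged with the app or the therapists: the bias is s(12) − s(0), which is not zero.
- Same mode in both arms at baseline and app in the IRG afterwards: s(0) = 0, and the whole of s(12) remains.

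**Step 3. Size of an uncancelled shift.** The article gives no figure for such a shift, so there is none to reproduce. The inputs are:

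- n = 20 per arm (section 2.8);
- n = 20 × (1 − 0.20) = 16 per arm with the 20% dropout named there;
- alpha = 0.05 (section 2.9), taken as two-sided because sidedness is not stated;
- an uncancelled shift b of 0.1 to 0.5 SD of the analysed score (assumption);
- no true effect.

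A two-sample t-test is used for illustration. It has 2n − 2 degrees of freedom and noncentrality b / √(2/n), where √(2/20) = 0.316 and √(2/16) = 0.354. The false-positive rate is the probability that a noncentral t variable falls outside the two-sided 5% limits.

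| Shift b (SD) | Noncentrality, n = 20 | False-positive rate, n = 20 | Noncentrality, n = 16 | False-positive rate, n = 16 |
|---|---|---|---|---|
| 0.1 | 0.32 | 6.1% | 0.28 | 5.9% |
| 0.2 | 0.63 | 9.5% | 0.57 | 8.5% |
| 0.3 | 0.95 | 15.2% | 0.85 | 13.0% |
| 0.5 | 1.58 | 33.8% | 1.41 | 27.8% |

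The rate is lower at 16 per arm only because the test is less sensitive. The bias in the estimate is b in both cases.

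**The case against.** The strongest reply is that the article can be read without contradiction. Section 2.3.1 may describe app entry in addition to the blinded assessment. Section 2.10 says where IRG data are stored, not who enters them, and a blinded assessor keying into an electronic form would satisfy both sections. This is conceivable, and it is why the point is an unreconciled description and not proof that blinding fails. But section 2.10 describes no such assessor record for the IRG, and nothing says which record would be analysed.

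The second reply is that the analysis removes a mode effect. It stands for a shift that is constant from baseline (step 2) and not for the other cases. A reader might infer that no analysis could remove any mode effect; that goes too far.

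The third reply is that participants know their treatment in both arms, so the rater of these outcomes is unblinded whatever form is used. That also stands. A common mode removes the difference in collection between arms, not all reporting bias.

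A reader might also infer further harms that the article does not support:

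- **Therapists see the scores.** Section 2.3.1.3 says that guiding clinicians view movement data; it does not mention outcome scores.
- **The analyst is unblinded by the data route.** Control data are transcribed to the same servers, no source field is described, and section 2.4 states that analysis is blinded.
- **Baseline is taken after allocation is known.** No section says so; the problem is only that sections 2.3.1 and 2.4 do not fit together.
- **Controls use paper.** The article says only CRF; paper is inferred from the transcription step.

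**Conclusion.** The point holds as an unresolved conflict. Sections 2.3.1 and 2.10 give an arm-specific route for outcome data, while sections 2.4 and 2.6 promise blinded assessment of everyone and baseline before randomisation. Followed as written, collection mode coincides with arm for NRS, WOMAC and SF-36. A shift that varies over time, or a mode change after baseline in the IRG alone, would then be inseparable from the treatment effect.

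The size is unknown. The range of roughly 6% to 34% at 20 per arm, or 6% to 28% at 16 per arm, depends on the assumed 0.1 to 0.5 SD of uncancelled shift, a two-sided test and no true effect. It illustrates sensitivity and does not predict what will happen.

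This should be fixed, but it does not undermine the trial. The affected outcomes are secondary, and the primary feasibility measures (willingness to take part, compliance, satisfaction) do not depend on this comparison.

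**What to change.** - Collect NRS, WOMAC and SF-36 in both arms with the same self-completed form, on paper or as a neutral electronic form outside FOR KOA, handed out by the blinded assessor. Self-completion keeps to the description of WOMAC in section 2.6.2.
- Complete the baseline form before the envelope is opened, and repeat it at weeks 6 and 12.
- Name this record as the one analysed. Remove outcome assessment from section 2.3.1 and keep the app for sessions, usage and satisfaction.
- Amend section 2.10 so that both arms have the same data route.
- State that participants are unblinded raters of these outcomes, so that the assessor-blinded label is not read as covering the ratings themselves.

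If a blinded assessment already runs alongside app entry, it is enough to say so, confirm that its mode is the same in both arms, and name the analysed record.

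The cost is protocol wording, some extra data entry, and assessor contact for 20 IRG participants at weeks 6 and 12, which section 2.6 already promises.

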#### Control group

2.3.2

Oral guidance including arthritis education, self-management and land-based exercise will be delivered from physicians and physiotherapists after the first assessment to the participants. Based on the specific situation of participants, the appropriate adjustments of the oral guidance will be made and recorded in a datasheet for analysis. In addition, the participants will be allowed to receive further intervention once the symptoms worsen. During the trial, the celecoxib and glucosamine hydrochloride are also required.

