### Withdraw

2.5

The participants in both groups can withdraw from the trial during the study. The researchers will notify the withdraw ones of potential adverse events and related managements, and record the withdrawal information, such as the reason, time and contact person.

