### Sample size

2.8

According to the previous statistical study, the recommended sample size of the feasibility trial is at least 12 in each group.^[50]^ 20 participants are recruited in each group and a total of 40 participants are recruited allowing for not less than 20% dropout rate of the period. The participants will help us to evaluate the mean and variability of the test results in order to provide plate beads for future larger scale research.

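### The response to worsening symptoms is worded differently in the two arms, which permits arm-specific loss and added treatment; the three sections need to be reconciled

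*Protocol article*

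**What the plan says.** Three sections of the protocol article bear on a participant whose symptoms worsen.

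- **Section 2.3.1 (IRG):** "Participants may terminate the trial at any time and receive relevant treatment in case of symptom deterioration"; the same sentence extends this to other unforeseen events. Leaving is optional, is mentioned together with treatment, and is not limited to worsening.
- **Section 2.3.2 (control):** "the participants will be allowed to receive further intervention once the symptoms worsen". Nothing is said about leaving the trial or remaining in it.
- **Section 2.5 (Withdraw):** "The participants in both groups can withdraw from the trial during the study". For those who do, staff will "record the withdrawal information, such as the reason, time and contact person". Assessment after withdrawal is not addressed.

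Section 2.6 sets the schedule: "Outcomes assessments will be conducted at baseline, 6 weeks and 12 weeks post-intervention". It adds that all participants will be assessed by blinded researchers and states no exception. Section 2.9 plans inferential comparison of the pain scale, WOMAC and SF-36, and lists dropout among the feasibility measures. The abstract also counts completion of the IRG programme within 12 weeks as a feasibility measure.

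**The concern.** One event, worsening symptoms, has two descriptions. In IRG the text pairs treatment with ending participation. In control it offers more treatment and is silent on participation. Site staff who follow each section as written could handle the same patient differently by arm.

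Two distortions could follow, and they pull in opposite directions. If worsened IRG participants leave and are not assessed, the remaining IRG mean looks better than it should. If worsened controls receive added treatment and remain, the control mean looks better than oral guidance alone would produce. The reader could not separate the two afterwards.

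The feasibility results are also touched. A completion or dropout figure means something different if worsening is an explicit route out in one arm and not in the other. Section 2.8 intends the trial to supply means and variability for larger research, and selective loss would distort both.

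**Working it through.** **1. The sections side by side**

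| Question | IRG (2.3.1) | Control (2.3.2) | Both arms (2.5) |
|---|---|---|---|
| Treatment on worsening? | Yes | Yes, described as further intervention | Not addressed |
| Leaving on worsening? | Explicitly permitted | Not mentioned | General right to withdraw |
| Assessed at 6 and 12 weeks after stopping? | Not stated | Not stated | Not stated |

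Sections 2.3.1 and 2.3.2 close with the same sentence on background medication, so wording shared between the arms is repeated where it applies. The worsening provision is not repeated; it is phrased differently.

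Recording differs too. IRG participants log other drugs in the app (2.3.1.2). In control, the datasheet in 2.3.2 is described for adjustments to the oral guidance, and no form is named there for the further intervention.

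**2. Figures the plan gives**

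The plan states no worsening rate and no effect of added treatment, so there is no figure of its own to reproduce on this point. Allocation is 1:1 (2.4). Section 2.8 gives 20 per group and dropout of not less than 20%, neither split by arm nor tied to worsening. Its starting point is that "the recommended sample size of the feasibility trial is at least 12 in each group". Inflating 12 for 20% dropout gives 12/(1 − 0.20) = 15. The planned 20 is compatible with those bounds and is not in dispute here.

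**3. Illustration of possible size**

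Assumptions: no true effect; outcome normal with SD 1; higher is worse; a fraction q of each arm worsens, and these are exactly the worst cases. The values of q are assumed. In an arm of 20, q = 5%, 10% or 20% is 1, 2 or 4 people.

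Removing the worst fraction q improves the mean of those left by φ(z₁₋q)/(1 − q):

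- q = 0.05: 0.1031/0.95 = 0.109
- q = 0.10: 0.1755/0.90 = 0.195
- q = 0.20: 0.2800/0.80 = 0.350

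If added treatment improves the worsened controls by r SD, the control mean improves by q × r. The apparent difference, in SD, is then:

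| Scenario | q = 5% | q = 10% | q = 20% |
|---|---|---|---|
| A. IRG loses its worst; controls all kept, r = 0 | 0.11 for IRG | 0.20 for IRG | 0.35 for IRG |
| B. As A, r = 0.5 | 0.08 for IRG | 0.15 for IRG | 0.25 for IRG |
| C. As A, r = 1 | 0.06 for IRG | 0.10 for IRG | 0.15 for IRG |
| D. Both arms lose the same share of worst cases | about 0 | about 0 | about 0 |
| E. Nobody leaves; only worsened controls get added treatment, r = 1 | 0.05 against IRG | 0.10 against IRG | 0.20 against IRG |

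Scenario A is the maximum for a given q, because real leavers will not be exactly the worst. Scenario E shows why the direction is unknown.

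**4. Against the precision of the trial**

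The 95% half-width for a difference in means, in SD units, is t × √(1/n₁ + 1/n₂):

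- 20 v 20: 2.024 × √0.1000 = 0.64
- 16 v 20: 2.032 × √0.1125 = 0.68
- 16 v 16: 2.042 × √0.1250 = 0.72

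A 20% loss in IRG alone leaves 16 v 20, so the matching comparison for 0.35 is 0.68, about half. The half-width of 0.64 assumes no loss at all and should not be set against a figure that requires loss.

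**The case against.** The strongest reply is that this is one safety provision loosely phrased twice. Both arms may withdraw under section 2.5, both have access to treatment on worsening, and the IRG wording is permissive. Section 2.6 says that all participants will be assessed, without exception. The primary outcomes are feasibility measures, mainly in IRG and not between-arm contrasts; pain, WOMAC and SF-36 are secondary. A journal article also commonly leaves follow-up after discontinuation and the analysis population to the full protocol or SAP.

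Much of this stands. Three stronger readings are tempting and are not supported:

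- **That worsened controls stay in the trial.** No section says so. It is an inference from silence in 2.3.2, and section 2.5 lets controls leave.
- **That the comparison is certainly biased.** Exit in IRG is optional and withdrawal is open to both arms. If both lose worst cases alike, the differential bias is about zero.
- **That 0.35 SD is the bias at the planned dropout.** That would place all of an allowance that section 2.8 does not split by arm on the worst IRG cases, with no control loss and no effect of added treatment.

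The point that survives is narrower. The article itself states two different provisions for the same event, and section 2.5 does not reconcile them. Silence on later assessment would be no finding alone. It matters here because ending the trial, in 2.3.1, can be read as ending assessment, while section 2.6 can be read the other way.

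**Conclusion.** The concern holds as an unreconciled difference in wording that permits differential loss and differential added treatment. It is not a rule that imposes them. Bias in the secondary between-arm comparisons is possible, and its direction cannot be settled from the documents.

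For losses of 5% to 20% confined to IRG, the upper end is 0.11 to 0.35 SD. This rests on a normal outcome, no true effect, leavers being exactly the worst, no control loss and no benefit from added treatment. Relaxing the last two assumptions reduces the shift, to near zero when both arms lose alike. Importance is moderate: the affected comparisons are secondary in a 40-person feasibility trial, although dropout and programme completion are also touched.

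**What to change.** 1. Reconcile sections 2.3.1, 2.3.2 and 2.5 so that one provision for worsening symptoms applies to both arms. Its content is for the clinicians.
2. State that stopping the assigned programme, or receiving further treatment, does not end the 6- and 12-week assessments unless the participant withdraws consent to follow-up.
3. Record the date and type of any further treatment in the same way in both arms.
4. Analyse participants in the arm to which they were randomised.

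The cost is protocol wording, one form field, and some effort to follow people who have stopped, at visits already planned. Assessments not made at 6 and 12 weeks cannot be recovered later.
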